#### Secondary outcome measurements

##### Visual Analogue Scale

The severity of menstrual pain will be measured with the VAS, a 100-mm horizontal line with endpoints from no pain on the far left to the worst possible pain on the far right. The VAS is scored by measuring in millimeters the distance from the side marked no pain to the edge of the mark made by the patient. Possible scores range from a minimum of 0 to a maximum of 100 mm, as participants will be asked to indicate a perception of pain intensity scored from one to 100. The VAS will be used during baseline measurements and during the first, second, third, fourth, fifth, and sixth menstrual cycle after inclusion.

##### Cox Retrospective Symptom Scale

The Cox Retrospective Symptom Scale (RSS) is a measurement of menstrual symptoms that has been shown to have high reliability, validity, and sensitivity [29]. It gives two scores: a Total Frequency Ratings score (RSS COX1) and an Average Severity Ratings score (RSS COX2). Lower scores indicate better health. The RSS will be used before treatment to assess the baseline condition of the patient.

##### Dysmenorrhea diary

The women will be provided with dysmenorrhea diaries to record the specific time of menstrual pain attacks, the duration of dysmenorrhea, the associated phenomena, and any medication used. This information will be recorded daily during every menstrual cycle of the three study periods. All patients will be carefully instructed on how to use this diary to rate their symptoms. The dysmenorrhea diary will be used during baseline measurements and during the first, second, third, fourth, fifth, and sixth menstrual cycle after inclusion.

##### Self-rating Depression Scale

The Self-rating Depression Scale (SDS) is a 20-item self-reporting questionnaire on the symptoms of depression. Subjects rate each item according to how they felt during the preceding seven days. Item responses are ranked from one to four. The sum of the 20 items produces a score between 20 and 80, with a score of greater than 40 suggesting clinically relevant depression [30]. The SDS will be used on the day when menstruation ends in the last month of the baseline period, and in the fourth menstrual cycle after inclusion (after completion of three sessions of treatment).

##### Self-rating Anxiety Scale

The Self-rating Anxiety Scale (SAS) has been widely used in research and in clinical practice for the detection of anxiety [31]. It also consists of 20 items rated on numerical values of one to four. The total SAS score may vary from 20 (no anxiety at all) to 80 (severe anxiety), with a value of greater than 40 suggesting the presence of a clinically relevant anxiety disorder. The SAS will be used on the day when menstruation ends in the last month of the baseline period, and in the fourth menstrual cycle after inclusion (after completion of three treatment sessions).

### Follow-up

The follow-up assessment is designed to evaluate the long-term effects of moxibustion. Upon completion of treatment, follow-up assessments will be conducted at the fourth, fifth, and sixth menstrual cycle after inclusion, lasting three menstrual cycles. In addition, patients will keep the daily dysmenorrhea diary and complete the CMSS and VAS measurements during every menstrual cycle in the follow-up period. Patients will send the relevant information to researchers immediately via email or short message service. To encourage participant compliance, we will show special solicitude for every participant and closely monitor the evolution of their illness.

### Statistical analysis plan

#### Data integrity

No record can be missed or omitted in the original data source. Any corrections should be explained in the appended notes signed and dated by the physicians participating in the clinical trial; primary entries are not allowed to be changed. After the observation of a clinical case, case report form (CRF) files will be submitted to the project directors for verification and signing by supervisors.

Data input will be done separately by two data collectors with computers and locked once the checking work is done. The data manager will clarify any questions regarding the CRF with the researchers through clinical supervisors. Researchers should answer any questions as soon as possible so that the data manager can conduct the modification, validation, and entry of the data.

#### Analysis

A statistician blinded to the whole trial process will perform the statistical analysis using the SAS statistical software package (Version 9.1, SAS Institute Inc.) in the Computer Integrated Manufacturing System. For the evaluation of curative effect in this trial, the per protocol set (PPS) will be used. The full analysis set (FAS) is determined according to an intention-to-treat population; all patients who are randomized and receive at least one treatment session will be included in the analysis set. The PPS is defined as the patients who complete the study and do not have major protocol violations. Demographic data and other basic indicators will be analyzed to test the balance of the three groups at baseline. The main indicators and global indicators will be analyzed within the FAS and PPS. The results will be described with the mean, standard deviation, median, P25 (Percentile 25), P75 (Percentile75), maximum, and minimum values of the differences between the treatment period and the baseline period. Between-group differences will be tested using repeated measure analyses of variance. The accepted level of significance for all analyses was *P* <0.05. Considering that the efficacy might be affected by factors such as age, age of menarche, and course of disease, all factors will be considered as co-variants for covariance analysis or logistic regression analysis when comparisons among groups are made. Missing data will be replaced according to the principle of multiple imputations.

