### Blinding

Double blinding of the clinician and patient is unfeasible owing to the unique nature of moxibustion operations. However, to ensure the integrity of the trial, the researchers will not assess the efficacy of treatment to avoid misleading the patients and inducing potential impacts on the compliance and outcome measurements. The therapist, the assessors of therapeutic effect, the data manager, and the statistician will be separated. Moreover, according to the principle of blinding, only patients allocated to the waiting list group will be told to wait for free treatments at the end of the study; allocation information will be strictly withheld from patients in the other two groups.

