#### Treatment group A (treated before menstruation)

Group A will be treated five days before expected menstrual onset and treatment will continue until menstruation begins. However, the subjects’ menstrual cycles may change and so the actual period of treatment will be five to seven days. The treatment will be the application of a moxa stick (herbal preparation with *Artemisia vulgaris*, Z32021062, Oriental Moxa Co., Suzhou, China) at acupoints SP6 and CV4 to patients in a supine position. The moxa roll is prepared by wrapping mugwort wool (herbal medicines may be mixed in it) with a piece of a paper. It is cylindrical, 1.5 cm in diameter, and 20 cm in length. A lighted moxa roll will be held 2.5 to 3 cm above the acupoint and moved upwards and downwards, to the left and right, or around. The patient should feel warmth but not scorching heat. Each point will be treated with moxibustion for five to 10 minutes.

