#### Control group C (waiting list group)

Participants in this group will receive no moxibustion-related intervention while the trial is in process. The subjects in this group will be asked to maintain their normal lifestyle, including diet, exercise, and workload. At the end of the trial, if participants in group C would like to be treated with moxibustion, we will offer free moxibustion treatment five times monthly for three menstrual cycles.

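### Curative effect is assigned to the per-protocol set, and no analysis of all randomised patients is made primary

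*Protocol article*

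**What the plan says.** All the statements on analysis sets are in the Analysis section of the protocol article.

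- Set for efficacy: "For the evaluation of curative effect in this trial, the per protocol set (PPS) will be used".
- Definition of that set: "The PPS is defined as the patients who complete the study and do not have major protocol violations".
- Definition of the FAS, which is described as following intention to treat: "all patients who are randomized and receive at least one treatment session will be included in the analysis set".
- Where the main outcomes are analysed: "The main indicators and global indicators will be analyzed within the FAS and PPS".
- Missing data: "Missing data will be replaced according to the principle of multiple imputations". No analysis set is named for this.

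Three other sections bear on the point.

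- Blinding: "Double blinding of the clinician and patient is unfeasible owing to the unique nature of moxibustion operations".
- Control group C: "Participants in this group will receive no moxibustion-related intervention while the trial is in process".
- Treatment group A: "Group A will be treated five days before expected menstrual onset and treatment will continue until menstruation begins". The next sentence of that section allows for changing cycles by letting the treatment period run from five to seven days.

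**The concern.** Only one sentence ties the efficacy conclusion to a single set, and it names the per-protocol set (PPS). Membership of that set is decided after randomisation. The trial asks whether moxibustion beats a waiting list and which timing is better. It states no non-inferiority margin, so it reads as a superiority trial, although the article does not use that word. In such a trial, removing dropouts and non-adherers tends to flatter the active arms.

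Several features make selection plausible here. Patients and clinicians are not blinded. Patients or their helpers apply the moxibustion at home (Interventions). The CMSS rates how bothersome the patient's own symptoms are, and in follow-up patients complete it and send it in themselves (Follow-up). Staying in the trial and keeping to the regimen can therefore depend on perceived benefit.

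The arms may also be selected differently. Group C has no moxibustion regimen to follow. Group B starts at an observed event, whereas group A starts from a predicted date, and the Discussion concedes that this date may be hard to predict. At stake are the efficacy claim against the waiting list and the timing comparison, where the planned difference is small.

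**Working it through.** **Which set decides?** Side by side, the sentences give three facts. The PPS is named for curative effect. The main indicators are analysed in both FAS and PPS. No sentence ranks the two or makes the FAS primary. Read literally, the PPS decides and the FAS is a second analysis.

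**Where can imputation act?** Patients who do not complete are outside the PPS by definition, so multiple imputation has little to fill in there. It could act in the FAS.

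**Would the FAS as written cure this?** It requires at least one treatment session. Group C receives no moxibustion until the trial has ended. Applied literally, the FAS would contain no controls.

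**Inputs for size** (Sample size section): expected CMSS means 1.7 (A), 1.9 (B) and 2.5 (C); effect size 0.2266; 74 randomised per group; 15% dropout. The SD is not printed.

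*The plan's effect size.* The mean of the three means is 6.1/3 = 2.033. The squared deviations are 0.1111, 0.0178 and 0.2178. Their average is 0.1156, with square root 0.340. Then 0.340/0.2266 = 1.50, so the stated effect size is reproduced with SD 1.5. (The stated power is not: 64 per group at this effect size gives 0.803, against the stated 0.90. That is a separate matter, and nothing below depends on it.)

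*Planned differences.* A versus B: 1.9 − 1.7 = 0.2. A versus C: 2.5 − 1.7 = 0.8.

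*Shift in a completer mean.* If a fraction d of one arm leaves, and those leaving are δ worse than the whole arm's average, the mean of those remaining looks better by δ × d/(1 − d). With d = 0.15 the factor is 0.15/0.85 = 0.1765. The values of δ are assumptions:

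| δ in SD | δ in points | Shift | Share of 0.2 | Share of 0.8 |
|---|---|---|---|---|
| 0.25 | 0.375 | 0.066 | 33% | 8% |
| 0.5 | 0.75 | 0.132 | 66% | 17% |
| 1.0 | 1.5 | 0.265 | 132% | 33% |

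These figures assume selective loss in one arm only. With equal d and equal δ in A and B, the shift in the A-B difference is zero.

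*A second route.* Assume no true effect. The 15% of an active arm highest on a latent tendency to leave drop out, that tendency correlates r with outcome, and the control arm loses 15% at random. The spurious benefit is r × φ(z)/0.85 × 1.5, with z = 1.036 and φ(z) = 0.233, which is 0.411 × r. For r = 0.2, 0.3 and 0.5 this gives 0.08, 0.12 and 0.21 points. With 74 × 0.85 = 62.9 per arm, the standard error of a difference is 1.5 × √(2/62.9) = 0.267. The two-sided 5% error for one pairwise comparison becomes about 6%, 7.5% and 12%. The values of r are also assumptions.

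**The case against.** The strongest reply is that an FAS analysis of the main indicators is planned and imputation has a place in it. That is correct. A reader might infer that efficacy is examined in completers alone and that imputation is bypassed altogether, and the Analysis section does not support that. Nor does it support a claim of two equal chances of success, since the only sentence that assigns efficacy to a set assigns it to the PPS. What stands is that no all-randomised analysis is primary. An unseen analysis plan could add detail, but it would have to contradict the printed sentence to cure this.

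A reader might also infer that early or late menses create violations in group A only. The documents do not support this. Major violations are not defined, the five-to-seven-day range makes room for shifting cycles, group B can miss days, and controls can fail to complete. Different selection in A and B is a possibility, not an established fact.

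On size, the table sets completers against the unknown full-arm mean, not the PPS against the FAS with imputation. Dropouts' later outcomes are unobserved in either set, and imputation recovers their deficit only as far as observed data predict it. The 132% figure is therefore a one-arm extreme and not the expected bias.

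Blinding also needs qualifying. The assessor and statistician are described as blinded, and the Blinding section says allocation information is withheld from the two moxibustion groups. Against that, the Randomization section has the envelope opened in front of the participant, and patients necessarily know whether and when they treat themselves.

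**Conclusion.** The concern holds in this form: the plan assigns curative effect to a set selected after randomisation, also lists an FAS analysis, and never makes an analysis of all randomised patients primary. This follows from the text and rests on none of the arithmetic.

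The direction of bias is a tendency, and its size cannot be known from the documents. Under the stated assumptions (SD 1.5 implied by the effect size, 15% lost, selective loss in one arm, deficits of 0.25 to 1.0 SD) the shift is 0.07 to 0.26 points. That is modest against the planned A-C difference but large against the planned A-B difference, so the timing question is the more fragile one if loss differs between A and B. It should be settled before results are seen, because it governs the primary conclusion.

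**What to change.** Change the Analysis section in three places.

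1. State that the primary CMSS analysis includes all randomised patients in the group to which they were assigned, with multiple imputation for missing values.
2. Remove the condition of at least one treatment session from the FAS definition, since group C cannot meet it during the trial.
3. State that the PPS analysis is a supporting sensitivity analysis that cannot replace the primary result, and delete the sentence that assigns curative effect to the PPS.

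The cost is wording in the analysis plan, with no added patients or visits. The estimated effect may be smaller than in the PPS. The primary result will also lean on the imputation model, which can recover only what the observed data predict about those who leave.

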**Methods/Design:**

This protocol is for a randomized controlled trial in which the assessor and statistician will be blinded. A total of 222 eligible patients with dysmenorrhea will be randomly assigned to three groups in a 1:1:1 ratio as treatment group A (treated before menstruation onset), treatment group B (treated at the onset of menstruation), or control group C (waiting list group). The participants assigned to the treatment groups will receive suspended moxibustion treatment at *Sanyinjiao* (SP6) and *Guanyuan* (CV4), while the waiting list group will not receive moxibustion treatment until the completion of the study. The trial period will consist of three baseline menstrual cycles, three menstrual cycles of treatment, and three menstrual cycles in the follow-up period. The primary outcome will be measured by changes in the Cox Menstrual Symptom Scale and the secondary outcomes will be measured using the Visual Analogue Scale, Cox Retrospective Symptom Scale, diary entries, the Self-rating Depression Scale, and the Self-rating Anxiety Scale. The safety of moxibustion will be assessed at every visit.

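### The full analysis set requires at least one treatment session, so no waiting-list participant can enter it and it is not intention-to-treat

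*Protocol article*

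**What the plan says.** The population rules are in the Analysis section, under the heading Statistical analysis plan. On principle: "The full analysis set (FAS) is determined according to an intention-to-treat population". On membership: "all patients who are randomized and receive at least one treatment session will be included in the analysis set". No exception is made for the control arm.

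The section on control group C says: "Participants in this group will receive no moxibustion-related intervention while the trial is in process". The Methods/Design part of the abstract agrees: "the waiting list group will not receive moxibustion treatment until the completion of the study". The free moxibustion offered to controls is optional and comes later; the sentence making the offer begins "At the end of the trial, if participants in group C would like to be treated with moxibustion".

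On use of the sets, the Analysis section says both "For the evaluation of curative effect in this trial, the per protocol set (PPS) will be used" and "The main indicators and global indicators will be analyzed within the FAS and PPS". The per-protocol set has its own rule: "The PPS is defined as the patients who complete the study and do not have major protocol violations".

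**The concern.** An intention-to-treat set is fixed by randomisation. This one is fixed by what happens afterwards, and the qualifying event is one that a third of the randomised women are designed never to have.

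There are two ways to apply the sentence, and neither gives an intention-to-treat set:

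- **Literally.** Group C is empty in the FAS. The efficacy of moxibustion against no treatment, a stated aim of the trial, cannot be estimated there.
- **Loosely, in groups A and B only.** Randomised women who never perform a session are removed from the treated arms, while all controls stay. Starting is a behaviour that follows allocation: treatment is done at home by the woman or a helper, there is no sham, and controls are told that they are waiting. If women who never start are less motivated or less well than the rest, removing them flatters moxibustion. The start rate could also differ between A and B, because A must start before a predicted onset that the Discussion admits is hard to predict, while B starts at an observed onset.

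The FAS matters more than usual here because the set named for judging efficacy is the per-protocol set. The FAS is the only safeguard against selective exclusion from that set.

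**Working it through.** **Inputs**

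- 222 randomised 1:1:1, at least 74 per arm (abstract; Sample size section).
- FAS entry: randomised and at least one session received (Analysis).
- Sessions received by group C during the trial: none (abstract; Control group C).
- Expected CMSS means: 1.7 for A, 1.9 for B, 2.5 for C; effect size f = 0.2266 (Sample size).
- Planned dropout: 15% (Sample size).

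**Step 1. Can a control receive a session under any reading of the article?** The visit schedule (Table 2) lists assessments, and no entry counts as a treatment session for group C. The Interventions section describes sessions only for the treated groups. The later free treatment falls after the trial. So the answer is no.

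**Step 2. Head count, literal reading**

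| Set | A | B | C | Total |
|---|---|---|---|---|
| Randomised | 74 | 74 | 74 | 222 |
| FAS as written | at most 74 | at most 74 | 0 | at most 148 |
| FAS as all randomised | 74 | 74 | 74 | 222 |

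Share of randomised women excluded by the wording alone: 74/222 = 33.3%.

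**Step 3. Which contrasts remain in the literal FAS?** The planned differences are C − A = 2.5 − 1.7 = 0.8, C − B = 2.5 − 1.9 = 0.6 and B − A = 1.9 − 1.7 = 0.2. The first two need group C and disappear. Only the 0.2 remains.

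The article gives no figure for the SD, but f implies one. The SD of the three means around their average of 2.033 is √[(0.333² + 0.133² + 0.467²)/3] = 0.340, so SD = 0.340/0.2266 = 1.50. For two groups, f = 0.1/1.50 = 0.067. The F-test noncentrality N·f² is 0.57 with 64 per group and 0.66 with 74 per group. Power at the 5% level is then 0.116 and 0.127. On the article's own assumptions, the one comparison left would very probably miss a real difference.

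**Step 4. Loose reading.** Let p be the share of a treated arm that never starts, μₙ the mean of those women and μₛ the mean of the starters. The all-randomised mean is (1 − p)μₛ + pμₙ, and the FAS mean is μₛ. The exclusion therefore shifts the arm mean by p(μₙ − μₛ).

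The article gives neither p nor μₙ, so what follows is an illustration. Take never-starters at the waiting-list mean of 2.5, starters at the planned treated means, and p anywhere from 0 to the whole 15% dropout allowance:

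- Women dropped per arm: 0 to 0.15 × 74 = 11.1.
- Group A: shift 0 to 0.15 × 0.8 = 0.12, so the difference from control is 0.80 in the FAS against 0.80 down to 0.68 among all randomised.
- Group B: shift 0 to 0.15 × 0.6 = 0.09, so 0.60 against 0.60 down to 0.51.

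The shift is larger if never-starters fare worse than untreated controls, and smaller or reversed if they fare better.

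**The case against.** The best reply is that this is a drafting slip. The same sentence invokes intention-to-treat, the section speaks of three groups, and the sample size rests on three means including the waiting list. The sentence also says who is included without saying that nobody else is. On this view no analyst would delete the control arm, so the 33% describes something that will not happen.

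The point about intent is probably right. It does not rescue the rule. A set definition that is not restrictive defines nothing, and keeping group C by common sense leads straight to the loose reading, which is not intention-to-treat either.

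Four further points deserve weight:

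- **The per-protocol set is unaffected.** It has no session condition, so controls stay in the set named for efficacy. This stands, and it limits the defect to the FAS.
- **The loose reading may cost little.** A woman is dropped only if she performs no session in any of three treatment cycles. No never-start rate is given, and the direction of bias depends on who those women are. This stands too.
- **Allocation is not cleanly open.** The Randomization section has the envelope opened in front of the participant, while the Blinding section says allocation is withheld from the two treated groups. The two statements conflict. Women in A and B nevertheless know that they are being treated, which is all the argument needs.
- **A rule worded alike for all arms need not exclude alike.** Requiring one post-randomisation CMSS, for example, could still lose more women from one arm than from another. This is a fair reason to prefer no condition at all.

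**Conclusion.** The concern holds. As worded, the FAS admits none of the 74 controls and at most 148 of 222 randomised women, so it yields no estimate of either treated arm against control. This follows from the article's text alone and rests on no statistical assumption. Under the more likely reading, controls are kept and never-starters are removed from A and B only, so the set is still not the intention-to-treat population that it is called. The size of that distortion cannot be derived from the article. In the illustration it runs from nothing to 0.12 CMSS points for A and 0.09 for B, and it depends on the assumed never-start rate and outcome.

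A control comparison survives in the per-protocol set. That leaves the trial's only control comparison under the literal wording in the set that removes non-completers and major violators. The sentence must be corrected before analysis.

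**What to change.** Replace the membership sentence with: *The FAS includes all randomised participants, analysed in the group to which they were assigned, regardless of whether any moxibustion session was performed.*

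Handle missing outcomes with the multiple imputation already planned. Preferably add no data condition. If one is wanted, it must be worded identically for all three arms and not depend on treatment. At least one post-randomisation CMSS is feasible, since Table 2 schedules that scale in every treatment and follow-up cycle. In that case report the number excluded per arm, because equal wording does not guarantee equal loss.

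The cost is one sentence, with no new data and no change in sample size. Women who never started enter the treated arms and dilute the estimate by p(μₙ − μₛ) as above. That is probably small, and it is part of what an intention-to-treat estimate is meant to include.
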